#### Stool Samples

Fresh morning stool samples were collected into plastic containers with a volume of 125 mL and tightly fitting lids. Samples were transferred to the laboratory in a cool box and worked up the same day. For the diagnosis of *S. mansoni* and soil-transmitted helminths, duplicate 41.7 mg Kato-Katz thick smears were prepared from each stool sample [22] and examined under a microscope. Infection intensities were expressed in eggs per gram of stool. For the diagnosis of *S. stercoralis*, the Baermann technique was employed, where an apricot-sized stool sample was placed on a gauze-lined mesh in a glass funnel equipped with a rubber tube and a clamp, covered with deionized water, and illuminated from below with a bulb. After 2-3 hours, the lowest 50 mL of the liquid was drained, centrifuged, and the sediment examined under a microscope for *S. stercoralis* larvae [22]. A separate stool sample was also collected in a self-administered manner by the participants (following the manufacturer’s instructions) using the OMNIgene.GUT tube, which contains microbial stabilizer.

### Pre-Analytic Processing of Biospecimens and Biobanking

DBS prepared on filter papers were sealed in air-tight bags containing dessicants and stored at -20°C in the Taabo laboratory. The DBS will be applied towards DNA and cytokine profiles. The DNA that will be extracted from the DBS (Whatman FTA cards) will facilitate research into genetic variations and DNA methylation [50]. EDTA blood was stored as 1.5 mL aliquots in cryotubes at -20°C in Taabo laboratory. Midstream morning urine specimens collected into sterile 9 mL vacuettes were stored as uncentrifuged and centrifuged 1.5 mL urine aliquots. Centrifugation was done at 1600 g and 4°C for 15 min [66], and the supernatant immediately aliquoted in cryotubes stored at -20°C in Taabo laboratory. Urine aliquots will be applied to metabolomics profiles and will be normalized to creatinine during the analytic process. Stool samples from the OMNIgene.GUT tube were stored in 0.5 mL aliquots in cryotubes at -20°C freezer in Taabo laboratory. These stool aliquots will be applied towards the metagenomic investigations of the gut microbiota.

DBS, blood, urine, and stool samples stored at -20°C in the Taabo laboratory (with the freezer being connected to a back-up generator) were transferred (on dry ice, on a weekly basis) to the Institut Pasteur de Côte d’Ivoire (IPCI) biobank for permanent storage at -80°C (Figure 3). On completion of the survey and therefore of biospecimen collection, the biobank will be mirrored as two identical banks hosted at IPCI (Abidjan, Côte d’Ivoire) and the Swiss Tropical and Public Health Institute (Swiss TPH; Basel, Switzerland). The mirroring of biobanks increases the safety of the biospecimens. Biomarkers derived from these “-omics” analyses can serve as exposure biomarkers, health-related phenotypes, or markers of susceptibility of exposures and diseases.

### In-Person Interviews

The in-person interviews were done using a tablet-based questionnaire in Open Data Kit format [67], lasting between 45 and 60 minutes. Questions covered demographic factors (eg, age, sex), water supply and sanitation facilities (availability and use), know-how, attitude, and behavior towards tobacco smoking, physical activity, obesity, alcohol consumption, and nutrition. They also included environmental risks (eg, exposure to mosquito coils, pesticides, indoor biomass fuels), gender, hormonal and reproductive factors, psychosocial stressors and resilience to them, disease symptoms (respiratory, cardiovascular, and diabetes), family history of disease, medical diagnoses and treatments, vaccination history, and access to health care.

### Data Management

Data from in-person interviews were collected using Open Data Kit, whereas health examination and laboratory data were collected as paper-based records, which are later uploaded into the Open Data Kit format. Data quality was assured through (1) formulation of standard operating procedures for all aspects of the study, (2) extensive and careful training of the study team according to the standard operating procedures, (3) onsite supervision of field activities ensuring adherence to protocol, and (4) continuous monitoring and internal evaluation of data entry during the field and laboratory work. Data collected on paper will be double-entered in two stages and later cross-checked to ensure accuracy and prevent data manipulation during or after the study. The software used will keep track of all changes made to the data. All data will be merged into a single database at the end of data entry using STATA version 14.0 (STATA Corporation).

### Data Analyses

The detailed CoDuBu data, enabled in part by HDSS routine data collected just before the start of this survey (Textbox 1), and the broad consent obtained from participants will allow us to test numerous hypotheses. The broad range of the CoDuBu research framework translates into a broad set of statistical methods. Analytical study plans or project proposals will be developed and submitted to statistical review at participating organizations. Collected data will include continuous and categorical variables. Results from the cross-sectional study will be described accordingly, reporting categorical variables as percentages with 95% confidence intervals, and continuous variables as medians with interquartile ranges. To explore associations between predictors and health outcomes, linear or logistic regression models will be used, as appropriate. Urban and rural differences in associations will be tested, as well as fixed and random effects study area models. Sampling weights will be applied to analyses to ensure a correct representation of the population. Missing data will be reported as separate categories and included in multivariable models. If full case analyses are performed, adjustment for data missingness will be done using appropriate methods for missing data imputation.

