**Methods:**

A baseline cross-sectional population-based survey was conducted over one year, in the Taabo health and demographic surveillance system (HDSS) in south-central Côte d’Ivoire. We randomly identified 1020 consenting participants aged ≥18 years in three communities (Taabo-Cité, Amani-Ménou, and Tokohiri) reflecting varying stages of epidemiological transition. Participants underwent health examinations consisting of NCD phenotyping (anthropometry, blood pressure, renal function, glycemia, and lipids) and infectious disease testing (infections with soil-transmitted helminths, schistosomes, and Plasmodium). Individuals identified to have elevated blood pressure, glucose, lipids, or with infections were referred to the central/national health center for diagnostic confirmation and treatment. Aliquots of urine, stool, and venous blood were stored in a biobank for future exposome/phenome research. In-person interviews on sociodemographic attributes, risk factors for infectious diseases and NCDs, medication, vaccinations, and health care were also conducted. Appropriate statistical techniques will be applied in exploring the concomitance of infectious diseases and NCDs and their determinants. Participants’ consent for follow-up contact was obtained.

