### Design

This was a population-based cross-sectional study among adult participants aged ≥18 years, randomly sampled within the selected Taabo HDSS areas. The examinations and interviews were conducted between April and August 2017. A biobank was established for future biomarker research based on biospecimens collected from the participants. The survey occurred in two phases.

Phase I (health examination; April and May 2017) took place over 2 days for each participant. The first day included obtaining informed consent, provision of materials and instructions for biospecimen collection (clean plastic container and OMNIgene.GUT tube (DNA Genotek Inc) for stool and BD Vacutainer urine collection system (Beckton, Dickinson & Co) for urine, at participants’ residences. The next morning, while participants underwent health examinations (at the health center) in a fasting state, fresh morning stool and urine samples collected at home were transferred cooled (~4°C) to the Taabo-Cité central laboratory for immediate pre-analytic processing. In the field, health examinations included point-of-care glucose, hemoglobin, HbA1c, lipids tests, anthropometry (height, weight, neck, arm, waist, and hip circumference), blood pressure, pulse, temperature, as well as preparation of dried blood spots (DBS) on filter papers. At the end of the examination, blood sample (stored at 4°C within 10 minutes of venepuncture) and DBS were sent to the laboratory for further processing. Multimedia Appendix 1 shows the detailed flow of the health examination in the field.

In the laboratory, blood samples were applied towards malaria diagnoses (rapid test and microscopy) and further aliquoted and stored (together with the DBS) in a -80°C biobank. Stool from the plastic container was analyzed for helminth eggs (or larvae), and urine was subjected to *S. mansoni* test and dipstick urinalysis (for blood, proteins, blood, glucose, urobilinogen, bilirubin, leucocytes, ketones, nitrites, pH, and specific gravity). Urine samples that tested positive for blood underwent a filtration method for *S. haematobium*. The remaining urine and OMNIgene.GUT-stabilized stool were aliquoted and transferred to the -80°C biobank. Case reporting and management of diagnosed IDs and NCDs were incorporated within the health examination period (Figure 3). Multimedia Appendix 2 shows the detailed flow of the laboratory work.

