### Sample Size Estimation and Sampling of Participants

For the descriptive cross-sectional study, using *Plasmodium* infection and diabetes as our disease co-occurrence of reference, we would expect a malaria prevalence of 30% [59] and diabetes prevalence of 6% [60] in adults. The expected prevalence of co-occurrence assuming independence was 2%. The health district of Tiassalé, where Taabo HDSS is located, has an estimated population of 200,000 [33]. Therefore, for a population of 200,000, with an error margin of 1%, a 95% confidence level, and an expected malaria and diabetes co-occurrence prevalence of 2%, we would need 751 participants. Assuming a nonresponse rate of 30%, the sample size becomes 976. A sample size of 1000 would therefore be enough for the descriptive baseline study.

A main hypothesis to be addressed in an envisaged, not-yet funded follow-up survey, would be that the average change in HbA1c would be higher in persons malaria-positive at baseline. For the power calculation, we assume a malaria positivity rate of 30% and a true difference in average change of HbA1c between malaria-positive and negative persons of at least 30% of the standard deviation (SD) sigma of individual changes. If these individual changes were normally distributed, this would mean that the median of change in malaria-positive persons coincides with the 62^nd^percentile in malaria-negative persons. Under this assumption, 560 persons being re-assessed for HbA1c at follow-up would provide a power of 90% to detect a statistically significant difference in the mean change of HbA1c between the two groups at the usual 5% level. However, a larger sample size is warranted in order to be able to compensate for potential reductions in statistical efficiency resulting from lower than expected malaria positivity prevalence or from variations in the prevalence of malaria-positivity or in the SD sigma across the three study sites. With 30% loss to follow-up, we would still have 700 persons to be re-assessed at follow-up, which would provide a moderate safety margin and allow for the adjustment of weak confounder variables. Therefore, the 1020 participants we sampled from the three selected areas of Taabo HDSS will enable adequate representation of the population and ensure enough statistical power to test our hypotheses.

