### Recruitment of Participants and Written Informed Consent

After an information event for the village population, informed consent from potential participants was obtained at their homes, in-person by HDSS field workers who are in close contact with the local population. In order to obtain written informed consent, the field workers explained the purpose, procedures, benefits, and potential harm of the study. The concept of establishing a biobank for future studies was also explained, and participants were made aware that their information would be treated in a coded manner to allow the establishment of a longitudinal study if they decided to participate. The voluntary nature of the study was explained to the participants. Participation in all or parts of the study, as well as nonparticipation was free of negative consequences. Sufficient time for asking questions on the aims and procedures of the study was provided to the participants. If a subject decided to participate, they signed the informed consent sheet. Illiterate participants put a cross in the presence of a literate witness. Consent for re-contact in the future was specifically obtained from all participants towards the establishment of a longitudinal cohort.

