Key health-related phenotypes in the CoDuBu study investigating the co-occurrence of common infectious diseases and noncommunicable diseases in Côte d’Ivoire.**A. Key phenotypes from the physical health examination:**Distribution of body temperature (auricular temperature)Distribution of height, weight, waist and hip circumference, prevalence of obesityDistribution of blood pressure and heart rate and prevalence of hypertension**B. Key phenotypes from the laboratory screening:**Prevalence of *Plasmodium* infectionPrevalence of urogenital schistosomiasis (*Schistosoma haematobium*)Prevalence of intestinal schistosomiasis (*S. mansoni*)Prevalence of species-specific soil-transmitted helminths (*Ascaris lumbricoides*, hookworm and *Trichuris trichiura*)Prevalence of *Strongyloides stercoralis*Prevalence of anemiaPrevalence of prediabetes/diabetesPrevalence of dyslipidemia**C. Key phenotypes from interview (>200 variables covering risk factors and effect modifiers):**Prevalence of doctor’s diagnoses/treatments, including HIV, tuberculosisPrevalence of health symptoms related to cardiovascular diseases, diabetes, respiratory diseases, and infectious diseasesDistribution of access to quality careDistribution of knowledge related to noncommunicable diseases and risk factorsPrevalence/exposure to noncommunicable disease risk factors: tobacco smoking, physical activity, nutrition, alcohol consumption, environmental exposures (air pollution from fossil fuels, occupational exposures, noise annoyance), gender/reproductive factors, stress, resilience, depression, and other psychosocial factors**D. Other variables derived from the Taabo health and demographic surveillance system database:**Sociodemographic factors (age, sex, nationality, ethnicity, marital status, pregnancy history, educational level, occupation, socioeconomic status assessed by a household-based asset index)Household characterization (size, water supply, sanitation and cooking facilities, building characteristics, and residential history)**E. Biobank:**Dried blood spots/aliquots from venous blood: genetic variation, DNA methylation, cytokine profileStool: gut microbiomeUrine: metabolome

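### Coding missing covariates as a separate category in the multivariable models leaves part of the confounding in the infection–NCD estimates, roughly in proportion to the fraction missing

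*Protocol article*

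**What the plan says.** The Data Analyses section gives two sentences on missing data. The first is the default: "Missing data will be reported as separate categories and included in multivariable models". The second is conditional: "If full case analyses are performed, adjustment for data missingness will be done using appropriate methods for missing data imputation". It names neither an imputation method nor the variables to be imputed.

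The models concerned are stated in the same section: "To explore associations between predictors and health outcomes, linear or logistic regression models will be used, as appropriate". The Design section makes clear that exposure is observed and not assigned: "This was a population-based cross-sectional study among adult participants aged ≥18 years, randomly sampled within the selected Taabo HDSS areas". Many candidate covariates come from the interview, which the textbox of key phenotypes describes as ">200 variables covering risk factors and effect modifiers". The interview took place on a separate third day, and the consent section allows partial participation: "Participation in all or parts of the study, as well as nonparticipation was free of negative consequences".

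Nothing restricts the separate-category rule to descriptive tables, to outcomes, or to covariates that are not confounders.

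**The concern.** A missing category looks harmless because it keeps every record in the model. In an observational analysis it has a cost. Where the confounder is known, the infection effect is estimated within its levels. Where it is unknown, all those records share one level, and the infection effect among them is crude. The model fits a single infection coefficient to both groups, so the reported value mixes an adjusted and an unadjusted association and is presented as adjusted. This does not require missingness to be informative.

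At stake are the infection–NCD association estimates. The Introduction cites earlier evidence pointing in both directions for helminths and diabetes, so a residual shift either way could be taken for a finding.

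**Working it through.** The article states no figure on missing data, so there is none to reproduce.

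**Inputs from the article.** Infection prevalence 30% and outcome prevalence 6% (Sample Size Estimation: "we would expect a malaria prevalence of 30% [59] and diabetes prevalence of 6% [60] in adults"); n=1020 (Abstract: "We randomly identified 1020 consenting participants aged ≥18 years in three communities").

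**Assumptions.** One binary confounder C, related to infection X and outcome Y by the odds ratios shown; C missing completely at random in a fraction m; true X–Y odds ratio 1 unless stated. C has prevalence 50% with outcome 6%, or prevalence 40% with outcome 24%.

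**Step 1: the model.** Let R=1 when C is missing. The fitted model is logit P(Y) = b0 + b1·X + b2·C·(1−R) + b3·R. With R=0 it adjusts for C. With R=1 it reduces to b0 + b3 + b1·X, and C is absent. One b1 serves both groups. The same reasoning applies to linear models.

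**Step 2: the crude association** (C prevalence 50%, odds ratios 3 and 3, outcome 6%).
- P(X|C=1)=0.411 and P(X|C=0)=0.189, average 0.30.
- P(Y|C=1)=0.0886 and P(Y|C=0)=0.0314, average 0.06.
- P(C|X=1)=0.5×0.411/0.30=0.685; P(C|X=0)=0.5×0.589/0.70=0.421.
- P(Y|X=1)=0.685×0.0886+0.315×0.0314=0.0706; P(Y|X=0)=0.421×0.0886+0.579×0.0314=0.0555.
- Crude OR=(0.0706/0.9294)/(0.0555/0.9445)=1.294 before rounding, although the truth is 1.

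**Step 3: what the missing category retains.** Approximately, ln OR = (1−m)·ln(adjusted OR) + m·ln(crude OR). With m=0.30: exp(0.30×0.258)=exp(0.077)=1.080. The exact large-sample fit gives 1.082.

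**Step 4: exact large-sample limits, true OR 1.**

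| C–X / C–Y odds ratios | C prevalence, outcome | 5% missing | 10% missing | 30% missing |
|---|---|---|---|---|
| 2 / 2 | 50%, 6% | 1.006 | 1.011 | 1.035 |
| 3 / 3 | 50%, 6% | 1.013 | 1.027 | 1.082 |
| 3 / 3 | 40%, 24% | 1.016 | 1.032 | 1.096 |
| 0.5 / 3 | 50%, 6% | 0.990 | 0.981 | 0.945 |

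With odds ratios 4 and 4 (40%, 24%) and 30% missing, the limit is 1.158. If C is unrelated to infection there is no bias (1.000). With a true OR of 1.5, odds ratios 3 and 3 (50%, 6%) and 30% missing, the limit is 1.622. Complete-case analysis returns the true OR in each exact-limit comparison made under this mechanism.

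**Step 5: type I error at n=1020, 30% missing.** Simulation of 3,000 datasets (odds ratios 3 and 3, outcome about 24%) gave 8.6% with the missing category and 5.0% with complete cases. Separate runs of 1,500 datasets with C prevalence 40% gave 9.7% (3 and 3) and 15.6% (4 and 4).

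A hand check uses SE ≈ 1/√[n·pX(1−pX)·pY(1−pY)].
- Outcome 24%: SE=1/√(1020×0.21×0.1824)=0.160. For OR 1.096 the shift is 0.0917/0.160=0.57, so the error is Φ(−1.39)+Φ(−2.53)≈8.8%. For OR 1.158 the shift is 0.1467/0.160=0.92, giving about 15%.
- Outcome 6%: SE=1/√(1020×0.21×0.0564)=0.288. For OR 1.082 the shift is 0.0788/0.288=0.27, giving about 5.9%.

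The 9–16% range therefore belongs to common outcomes. For diabetes at 6% the odds ratio is shifted similarly, but wider standard errors hide most of the effect on type I error.

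**The case against.** The strongest case on the other side is about size and reach, and much of it stands.

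- **No missing fraction is given.** A reader might infer from the consent wording and the separate interview day that missing covariates will be common. The consent sentence is a statement of voluntariness, not a forecast. The Results section reports questionnaire administration completed, and the Discussion reports little difficulty.
- **Important confounders may be nearly complete.** Age, sex, ethnicity, education, occupation and the asset index come from the HDSS database, and HDSS registration was an inclusion criterion. The rule bites mainly on interview covariates, whose confounding beyond these may be weaker than odds ratios of 3 to 4.
- **Missing stool or blood is a different problem.** Those samples mainly supply exposures and outcomes. The mechanism shown here concerns missing confounders.
- **Continuous covariates need not be categorised.** A constant fill-in plus an indicator keeps them continuous, so that charge cannot be made from the text.
- **The two sentences are not a proven contradiction.** A reader might take *full case* to mean complete case, in which nothing is left to impute. It could equally mean an analysis of the full sample obtained by imputation. The wording is ambiguous.
- **The association models are exploratory.** Later analysis plans are to undergo statistical review, and the baseline sample size is a precision calculation for co-occurrence.

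None of this removes the point. The article states the rule affirmatively, for models in which confounding is expected. Later review of individual plans does not withdraw a stated default, and a conditional imputation sentence does not replace it.

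**Conclusion.** The point holds as a should-fix. The stated default biases infection–NCD association estimates even under the most benign missingness, by about the missing fraction of the affected covariate's confounding on the log-odds scale. With a true OR of 1, that means about 1.01–1.03 at 5–10% missing with confounder odds ratios of 2 to 3, and about 1.08–1.16 at 30% missing with odds ratios of 3 to 4. Where the confounder is inversely related to infection, the limit falls below 1 (0.945 in the case shown). Type I error of about 9–16% requires 30% missing, strong confounding and a common outcome. At 20% missing, simulated values were only 6.1–6.2%.

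These sizes rest on one binary confounder, assumed odds ratios and an assumed missing fraction. A reader might infer that confounding is left uncontrolled altogether. The calculation does not support that: adjustment fails only in the affected records, and only for covariates related to both infection and outcome. Prevalence and co-occurrence estimates do not depend on this rule.

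**What to change.** Confine the missing category to descriptive tables. In the association models, handle missing covariates by multiple imputation, with the outcome, infection status, site, sampling weight and HDSS variables (age, sex, education, asset index) in the imputation model. Report complete-case results as a sensitivity analysis. Reword the *full case* sentence to say which analysis is imputed and which is not.

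Multiple imputation was not simulated here, and complete-case analysis alone removes the bias under missing completely at random. The reasons to prefer imputation as the main method are that it keeps all records (30% missing on one covariate would leave 1020×0.70=714) and allows missingness to depend on observed variables. The cost is modest extra analysis work and reliance on a missing-at-random imputation model. No new data are needed.
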